**Fig. 3 Fig3:**
[figure not shown]
Controllable treatment chair

**Fig. 4 Fig4:**
[figure not shown]
Seated lumbar rotation manipulation (flexion, rotation, and pulling)

The manipulators are trained doctors. They will receive a 2-week training, and the clinical research can only be carried out after they pass the examination of the chief physician.

#### Lumbar traction in supine position control group

The operation of the lumbar traction in supine position [21] treatment method is as follows: the patient is in supine position with the chest band fixed in both armpits and the pelvic band fixed in the upper edge of the iliac crest. The tightness of binding is moderate. The traction weight starts from a small amount and increases to 50% of the patient’s weight. During traction, a triangular brace is placed in the lumbosacral part of the patient, which is located at the lower edge of the lumbar sliding instability segment. It will be taken once a day, 5 times a week, 30 min each time.

Implementing seated lumbar rotation manipulation and lumbar traction in the supine position group will not require alteration to usual care pathways (including use of any medication) and these will continue for both trial arms.

### Outcome assessment

Variables for this clinical trial included the patient’s baseline, primary, and secondary outcomes.

The baseline will be completed before treatment, and the primary and secondary results will be measured at baseline and on the 1st, 3rd, 5th, 8th, 10th, 12th, 15th, 17th, and 19th days after the first treatment, and followed up at the 1st, 3rd, and 6th months. All primary and secondary outcomes will be evaluated by experienced doctors at Wangjing Hospital, and patient allocation results will be blind to them.

#### Basic information

Researchers will use a self-designed questionnaire to collect participants’ demographic characteristics (such as gender, age, education, marital status, height, and weight) and medical history.

#### Primary outcomes

We will use the Japanese Department of orthopedics Association (JOA [14]) low back pain rating scale (Table 1) to observe and record the symptom and sign scores of the two groups of patients at each visit point. The parameters in the scoring table are divided into four parts. The maximum score is 29 points, and the minimum score is −6 points. The higher the score the more normal the patient’s overall status. VAS [15] will be used to observe and record the pain degree of each visiting point in the two groups (Fig. 2), which means marking the numbers 0–10 with a straight line divided into 10 equal parts, according to the patient’s degree of pain to determine and draw on the corresponding number, and finally by the doctor according to the patient’s mark on the scale of the number to score. If the patient is marked on 5, it will be recorded as 5 points.

#### Secondary outcomes

JOA [14] efficacy evaluation standard will be used to evaluate the overall efficacy as the secondary outcomes, which is the calculation of treatment improvement rate. Treatment improvement percentage= (post-treatment score) − (pre-treatment score)/(29 −(pre-treatment score)) × 100%. When the improvement rate is 100%, means it is cured; more than 60%, effective; 25–60%, effective; and less than 25%, invalid.

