**Table 1 Tab1:**
[figure not shown]
Schedule of enrolment, interventions, and assessments

**Table 2 Tab2:** The JOA [14] scoring system for assessment of low back pain. The score in a normal subject is the total of the best scores: (I+II+III+IV) = 29 points

Parameter	Finding	Score (points)
I. Subjective symptoms (9 points)		
a. Low back pain	None	3
	Occasional mild pain	2
	Frequent mild/occasional severe pain	1
	Frequent pain/continuous pain	0
b. Leg pain and/or tingling	None	3
	Occasional slight symptoms	2
	Frequent slight symptoms/occasional severe symptoms	1
	Frequent severe symptoms/continuous severe symptoms	0
c. Gait	Normal	3
	Able to walk > 500 meters although it results in pain tingling and/or muscle weakness	2
	Unable to walk > 500 meters owing to leg pain tingling and/or muscle weakness	1
	Unable to walk > 100 meters owing to leg pain tingling and/or muscle weakness	0
II. Clinical signs (6 points)		
a. Straight leg raising (includes a tight hamstring)	Normal (> 70°)	2
	30° to 70°	1
	< 30°	0
b. Sensory disturbance	None	2
	Slight disturbance (not subjective)	1
	Marked disturbance	0
c. Motor disturbance	Normal (Grade 5)	2
	Slight weakness (Grade 4)	1
	Marked weakness (Grades 0 to 3)	0
III. Restriction in activities (14 points)		
a. Turn over while lying	No restriction	2
	Moderate restriction	1
	Severe restriction	0
b. Standing	No restriction	2
	Moderate restriction	1
	Severe restriction	0
c. Washing	No restriction	2
	Moderate restriction	1
	Severe restriction	0
d. Leaning forward	No restriction	2
	Moderate restriction	1
	Severe restriction	0
e. Sitting about 1 h	No restriction	2
	Moderate restriction	1
	Severe restriction	0
f. Lifting or holding a heavy object	No restriction	2
	Moderate restriction	1
	Severe restriction	0
g. Walking	No restriction	2
	Moderate restriction	1
	Severe restriction	0
IV. Urinary bladder function (−6 points maximum)	Normal	0
	Mild dysuria	-3
	Severe dysuria	-6

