### Statistical analysis

An independent statistician will use the SPSS V.25.0 software to perform the statistical analysis. Count data and grade data will be described by the number of case. The counting data will be tested by χ^2^; Wilcoxon rank-sum test will be applied to rank data. The measurement data will be statistically described with mean ± standard deviation. In group comparison, paired sample t-test will be applied. The rank sum test will be used for the difference comparison between groups. *P* < 0.05 will be considered statistically significant.

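### The JOA improvement-rate formula lacks a bracket around the score difference, and two of its four response bands share the label 'effective'

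*Protocol article*

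**What the plan says.** Under Secondary outcomes, the Protocol article lists one outcome: "JOA [14] efficacy evaluation standard will be used to evaluate the overall efficacy as the secondary outcomes, which is the calculation of treatment improvement rate". The derivation is printed as "Treatment improvement percentage= (post-treatment score) − (pre-treatment score)/(29 −(pre-treatment score)) × 100", followed by a per cent sign. The grading rule comes next: "When the improvement rate is 100%, means it is cured; more than 60%, effective; 25–60%, effective; and less than 25%, invalid".

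Two other places fix the scale. Primary outcomes states "The maximum score is 29 points, and the minimum score is −6 points", and the caption of Table 2 states "The score in a normal subject is the total of the best scores: (I+II+III+IV) = 29 points". Statistical analysis says that count and grade data are described by numbers of cases and that "Wilcoxon rank-sum test will be applied to rank data". The Abstract and Study design mention the JOA efficacy standard but do not restate the formula or the grade names.

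**The concern.** There are two separate defects in the same short paragraph.

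First, the printed brackets enclose each score singly and never the difference, so the division acts on the pre-treatment score alone. An improvement rate should be the share of the possible gain that was achieved: 0% for no change and 100% for a return to the best score. The printed expression has neither property.

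Second, "more than 60%, effective; 25–60%, effective; and less than 25%, invalid" gives two adjacent bands one name. A cut-off at 60% serves no purpose unless it separates two grades, so either one label is wrong or the cut-off is redundant. The text does not say which.

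At stake is the overall-efficacy result. A derivation programmed literally from the article would misgrade most patients. Even with the formula corrected, the number of ordered grades would remain open to choice after the data are seen.

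**Working it through.** **Inputs.** Best JOA score 29 and minimum −6 (Primary outcomes; Table 2 caption). Anchor: 100% means cured (Secondary outcomes). Bands: 100%, above 60%, 25–60%, below 25% (Secondary outcomes). 'Cured' is taken here as a return to 29. The pre and post scores below are chosen for illustration.

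**Three ways to evaluate the rate.**
- Strict precedence: post − [pre/(29 − pre) × 100].
- Whole expression as a percentage: [post − pre/(29 − pre)] × 100%.
- Difference bracketed: [(post − pre)/(29 − pre)] × 100%.

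**Check against the article's own anchor (pre 15, post 29).** Here 15/(29 − 15) = 15/14 = 1.0714.
- Strict precedence: 29 − 107.1 = −78.1.
- Whole expression: (29 − 1.0714) × 100% = 2792.9%.
- Difference bracketed: 14/14 × 100% = 100%.

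Only the bracketed form reproduces the stated 100%.

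**Further cases.**

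| Pre | Post | Strict precedence | Whole expression | Difference bracketed |
|---|---|---|---|---|
| 15 | 10 (worse) | −97.1 | 892.9% | −35.7% |
| 15 | 15 (no change) | −92.1 | 1392.9% | 0% |
| 15 | 18 | −89.1 | 1692.9% | 21.4% |
| 15 | 22 | −85.1 | 2092.9% | 50.0% |
| 15 | 25 | −82.1 | 2392.9% | 71.4% |
| 15 | 29 (full recovery) | −78.1 | 2792.9% | 100% |
| 20 | 26 | −196.2 | 2377.8% | 66.7% |

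Under strict precedence every row is below 25%, including full recovery. Under the whole-expression reading every row is above 60%, including the patient who got worse. With the difference bracketed, post scores of 18, 22, 25 and 29 from a pre score of 15 fall one into each printed band.

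**All integer scores.** Pre from −6 to 28 (35 values) and post from −6 to 29 (36 values) give 35 × 36 = 1260 pairs. The printed expression gives the same band as the bracketed form in 783 pairs under strict precedence and in 556 under the whole-expression reading. For pre scores 5 to 28:
- Under strict precedence every pair falls below 25%, including all 24 full recoveries.
- Under the whole-expression reading, 23 of the 24 no-change patients fall above 60%.

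These counts weight all score pairs equally. They are not a forecast for trial patients.

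**Labels.** With the formula corrected, the (15, 22) patient has 50.0% and the (15, 25) patient 71.4%. By name both are 'effective'. With four grades they occupy different ranks and different rows of the table; with three they are tied and counted together.

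**The case against.** The strongest reply is that nobody would be misled. The article calls the quantity an improvement rate, fixes 29 as the best score and ties 100% to cure. The 29 − pre denominator is printed, and the literal values are visibly absurd. The intended form can therefore be recovered. This stands: a reader might infer that the outcome cannot be computed, but the text does not support that.

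A reader might also drop the factor of 100 and compare raw results with the percentage cut-offs. For example, 26 − 20/9 = 23.8 might be read as 23.8%, moving a patient whose bracketed rate is 66.7% below 25%. That mixes units. The same expression is 2377.8% as a percentage, or −196.2 under strict precedence.

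On the grades, the numeric cut-offs do separate four ordered bands, so a rank test can be run on them. It would go too far to say that the article merges the two middle bands; it only fails to name them apart. The link to the rank-sum test is also an inference, because Statistical analysis does not name the outcome to which that test applies. That 100% also exceeds 60% is a small matter, since the list takes 100% out first.

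Finally, a reader might ask which visit the grade is analysed at. That is commonly left to an analysis plan or full protocol, neither of which is shown, and it is no part of this point.

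What remains is that the article states the derivation explicitly, states it wrongly, and nowhere corrects it or resolves the duplicate label.

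**Conclusion.** The point holds as a wrongly printed outcome rule with an ambiguous grading scheme, of moderate to minor severity. Literally applied, the formula misses the article's own 100% anchor by a wide margin (−78.1 or 2793% for full recovery from 15) and does not return 0% for no change. The duplicate label leaves three or four grades possible, which can change ranks and response counts. By how much cannot be said without data.

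The conclusion assumes that cured means a JOA score of 29 and that the grades are to be counted or ranked. It does not show that patients will in fact be misgraded, since the intended formula can be inferred. The directly analysed JOA and VAS scores, the sample size of 60 and the 0.05 significance level do not depend on it.

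**What to change.** In Secondary outcomes, print: improvement rate = [(post − pre)/(29 − pre)] × 100%.

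Replace the grading sentence with four mutually exclusive, ordered and distinctly named grades:
- 100%
- more than 60% and less than 100%
- 25% to 60% inclusive
- less than 25%, including negative values

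Check that the derivation program uses the same formula and the same four grades. The cost is a short text correction and that check. No change to data collection, sample size or the primary analysis follows.

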### Safety measurements

During the intervention period, researchers will monitor the occurrence of adverse events; observe the type, degree, and incidence of adverse events; and record and handle them. If there are any adverse events, such as trauma, the adverse event case report form (CRF) will be used for detailed reporting. In addition, the researchers will specifically note the causal relationship and severity of adverse events in the evaluation of seated lumbar rotation manipulation intervention. If serious adverse events occur, they will be reported to the ethics committee.

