## Method/design

### Study design

According to the random number table method [13], a total of 60 patients with DLI will be divided into sitting lumbar rotation manipulation group (the intervention group) and supine lumbar traction group (the control group), 30 cases in each group. DLI patients will be numbered according to the visit time, and any one number in the random number table will be selected as the starting point. A random number corresponding to each patient will be obtained along the same direction. Divide this number by 2, and the remainder of 0 will be the intervention group, and the remainder of 1 will be the control group. Two residents participating in this study will be responsible for generating the allocation order sequence.

The treatment of the two groups lasted for 3 weeks. The manipulation of the intervention group would be carried out once every other day, three times a week, a total of 9 times; the control group would be given lumbar traction once a day, five times a week, a total of 15 times. JOA [14] and VAS [15] scores will be recorded as the primary outcomes before the treatment and at the 1st, 3rd, 5th, 8th, 10th, 12th, 15th, 17th, and 19th days after the first treatment and follow-up visit at the 1st, 3rd, and 6th months. JOA [14] efficacy evaluation standard will be used to evaluate the overall efficacy as the secondary outcomes. When analyzing the results, the personnel who collect the data are blind to the grouping situation. The flow of this clinical trial is shown in Fig. 1; the schedule of enrolment, assessments, and interventions is presented in Table 1. JOA [14] and VAS [15] scores are presented in Table 2 and Fig. 2.

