### Data collection and management

The outcome assessors will use the CRF papers to collect the data. The CRF papers will be randomly put into envelopes of different groups and sent to a researcher who is responsible for electronic data input. Then, the researcher will transcribe the CRF into an electronic data acquisition system (EDC), which is a free Research Manager named ResMan (http://www.medresman.org) provided by the China Clinical Trial Registry and meets the available standards for security. Every subject will be assigned a separate experiment identification number, and the relevant data will be strictly confidential. Only members of the trial will have access to the data set. Anonymized trial data will be shared with other researchers to enable international prospective meta-analyses. The research data will be stored in the EDC system in a separate password-protected location. Data Monitoring Committee was not considered as this is a low-risk intervention.

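### Adverse-event monitoring is stated for the 3-week treatment period although both arms are seen to month 6, and causality is worded for manipulation with no counterpart for traction

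*Protocol article*

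**What the plan says.** The Safety measurements section opens its plan with "During the intervention period, researchers will monitor the occurrence of adverse events". It continues that staff will "observe the type, degree, and incidence of adverse events; and record and handle them". It then provides an adverse-event form for any event, adds that "the researchers will specifically note the causal relationship and severity of adverse events in the evaluation of seated lumbar rotation manipulation intervention", and sends serious events to the ethics committee.

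Study design fixes the length of treatment: "The treatment of the two groups lasted for 3 weeks". The same section plans a "follow-up visit at the 1st, 3rd, and 6th months", and Outcome assessment repeats that patients are "followed up at the 1st, 3rd, and 6th months". Those later visits are described for the primary and secondary outcomes. The readable text does not mention adverse events at them.

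The section on randomisation and blinding says that doctors and patients cannot be blinded, while the outcome evaluator and the statistician are. On oversight, Data collection and management says: "Data Monitoring Committee was not considered as this is a low-risk intervention".

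**The concern.** Benefit is measured over six months, but the stated window for harm closes at three weeks. A delayed problem, such as a new neurological complaint at month 2, would have no stated route onto an adverse-event form, even though the patient attends at month 3.

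The second difficulty is attribution. The only sentence on causality refers to manipulation. Traction is an active control with 15 sessions, and nothing says that relatedness to traction will be judged. If relatedness is assessed for one arm only, by staff who know the allocation, a table of treatment-related events by arm would reflect the assessment rule as well as the treatments.

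Both matter because the trial would be a natural source for statements about the safety of this manipulation, and the protocol already calls the intervention low-risk. Information not asked for at a visit is hard to recover later.

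**Working it through.** **Plan's own figures.** The plan gives no figure for the share of follow-up under adverse-event monitoring, so there is none to reproduce. Its session counts do reproduce and confirm the 3-week period: 3 × 3 = 9 manipulations and 5 × 3 = 15 traction sessions.

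**Share of follow-up with stated monitoring.**

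Inputs from the protocol: treatment of 3 weeks = 21 days; last on-treatment assessment on day 19; last visit at month 6.

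Assumptions, because the protocol does not state them: a month is 30 or 30.4375 days, and the months run either from the first treatment or from the end of treatment.

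Formula: share = monitored days / total follow-up days.

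| Months counted from | Follow-up (days) | 19-day window | 21-day window |
|---|---|---|---|
| First treatment | 6 × 30 = 180 | 10.6% | 11.7% |
| First treatment | 6 × 30.4375 = 182.6 | 10.4% | 11.5% |
| End of treatment | 180 + 21 = 201 | 9.5% | 10.4% |
| End of treatment | 182.6 + 21 = 203.6 | 9.3% | 10.3% |

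The range is about 9 to 12%, which leaves about 88 to 91% of follow-up without stated monitoring.

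**What is and is not the same in the two arms.**

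| Element of Safety measurements | Arm named? |
|---|---|
| Monitoring of occurrence | None |
| Type, degree and incidence | None |
| Adverse-event form | None |
| Serious events to the ethics committee | None |
| Causal relationship, with severity mentioned again | Manipulation |

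Degree is in the general list, so severity is covered for both arms. Causality alone has no general counterpart. The asymmetry is therefore in judging cause, not in finding or grading events.

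**What the month 1, 3 and 6 visits would still show.** JOA scores leg symptoms, gait, sensory and motor disturbance and bladder function, and VAS scores pain. Marked worsening would be visible to some extent. But a score carries no onset date, relatedness or outcome, and a total can hide a loss. A fall from 2 to 1 on motor disturbance together with a rise from 0 to 2 on standing gives a net change of −1 + 2 = +1, an apparent improvement.

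**The case against.** The best defence has five parts.

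- *Nothing forbids later recording.* True. That monitoring stops at week 3 is inferred from the wording. The schedule in Table 1 could not be read in the copy reviewed, and an article condenses the full protocol. This stands as a limit on certainty. But the text does state a window, and that window is shorter than follow-up. If Table 1 lists adverse events at the later visits, text and table need to be reconciled.
- *The causality sentence may describe the whole trial as an evaluation of manipulation.* Possible, and the sentence is worded as an addition to the general recording. On either reading, relatedness to traction is not provided for.
- *The exposure falls inside the window.* True. The 9 to 12% is a share of calendar time, not of risk, and early events may well dominate.
- *Later visits are not empty of safety information.* Also true. A reader might infer that the trial is blind to harm after week 3, or that adverse-event reports are its only safety data. The JOA neurological and bladder items and VAS, scored by blinded assessors, contradict both. The serious-event sentence has no time limit of its own, and withdrawn patients are to be observed for a further, undefined period. The absence of a monitoring committee does not change this, because a committee reviews data and does not generate them.
- *Ascertainment during treatment covers both arms.* This stands in full. A reader might infer that the whole safety comparison is one-sided or uninterpretable. The document does not support that, because every element except causality is worded without an arm.

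**Conclusion.** The point holds in a limited form. As written, adverse-event monitoring is tied to the 3-week treatment period, about 9 to 12% of follow-up under the stated assumptions on month length and origin. Harms arising later would appear only indirectly in JOA and VAS and would not be recorded as events. Causality is explicitly noted only in the evaluation of manipulation, so with unblinded treating staff a comparison of treatment-related events between arms would not be fair. The incidence and degree of events during treatment can be compared.

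The small sample is a separate matter. With 0 events in 30 patients, the one-sided 95% upper limit is 1 − 0.05^(1/30) = 9.5%. That follows from the arm size and would be the same with perfect collection, so it does not measure this defect. It does show that claims of low risk will rest on sparse data in any case. The efficacy results and the sample size are not affected.

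**What to change.** Amend Safety measurements so that:

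- adverse events are collected from randomisation to the month 6 visit, with the same form and the same questions in both arms, including at months 1, 3 and 6;
- severity and relatedness to the allocated treatment, whether manipulation or traction, are recorded for every event;
- events are reported by arm and by period (during treatment, after treatment).

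Bring Table 1 into line with the amended text. Extending the window takes it from 19–21 days to about 180–204 days, on the same assumptions about the months.

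The cost is one extra form at three visits that already take place, and a little more data entry. An added page would not detect changes visible only on imaging, since the text describes no follow-up imaging among the outcomes.
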